### Main objective

Compare the number of hospitalizations due to anaemia of patients receiving monthly capillary Hb measurements and those receiving standard venipuncture monitoring.

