### Intervention

The Hb levels of participants in the intervention group will be taken once a month with a Veri Q® haemoglobinometer, that showed good performance data, in accuracy test compared with the reference value from Nihon Kohden MEK-6420 (R2 = 0.9881) and with the Sysmax reference value (R2 = 0.9968) [21]. If a patient’s haemoglobin level falls below their reference value, the nurse case manager will activate the transfusion circuit by scheduling an urgent referral to the day hospital, an outpatient service where short-term treatment and diagnostic tests are performed. The interdisciplinary team at this unit will prescribe and administer the transfusion and handle the hospital discharge, in a specific circuit between health levels created to this intervention.

The WHOQOL-BREF questionnaire on quality of life will be administered at the first visit and six and 12 months.

To know the satisfaction with the intervention, a single item survey will be administered upon inclusion in the study and six and 12 months. The question is “to what extent are you satisfied with your anemia control”, and the possible answers are not satisfied, satisfied and very satisfied.

An ad hoc satisfaction survey on the intervention will be administered upon inclusion in the study and six and 12 months.

Participants in the control group received standard monitoring, the frequency of which is variable, since it is determined by clinical criteria. The data will be collected by reviewing patients’ computerized clinical records and a bimonthly phone call to determine how many times they have been hospitalized and visited the A&E during the study period. The WHOQOL-BREF questionnaire on quality of life will be administered at the first visit and six and 12 months of inclusion in the study. Data will also be collected for the control group.

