### Criteria for suspending or modifying the interventions assigned to each subject in the trial

Participants can leave the study at any time and may withdraw consent.

They will be excluded from the trial in the following cases:Death.They wish to leave the study.Palliative care is initiated and transfusions are rejected.

During the trial, patients in the control group may not have their capillary Hb levels measured.

No risks are anticipated for patients by participation in this study.

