### Statistical analysis

Statistical analyses will be conducted on a blinded intention-to-treat basis, with all participants who were initially randomised into the study included where data are available for each measurement time point.

Univariate descriptive statistics:

The main numerical variables will be described by measures of centrality and dispersion or absolute and relative frequencies in the case of categorical variables. Univariate comparisons between the intervention group and control group will be performed using mean comparison tests (T-test or similar) or distribution comparison tests (Chi-squared or similar).

Predictive model:

The result variables will be considered discrete quantitative variables. Multiple linear regression will be used to model the data collected, taking those that present significant differences in the previously calculated univariate models as independent variables, in addition to the demographic and clinical variables considered relevant.

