### Expected results

#### The main result variables are

Number of hospitalizations due to anaemia.Number of A&E visits due to anaemia.Time elapsed between Hb measurement and circuit activation.Time elapsed between Hb measurement and when the transfusion is performed.Time elapsed between Hb measurement and return home.

The specific measurement variable is the Hb level taken with the Veri-Q® haemoglobinometer once a month.

Other variables are:Satisfaction with monthly anaemia monitoring: taken at six and 12 months. Ad hoc questionnaire.Quality of life: measured at the start of the study and six and 12 months. WHOQOL-BREF questionnaire [22, 23].Prescribed medication that might alter Hb or haematocrit levels.Signs and symptoms of anaemia at monthly visits (dyspnoea, asthenia, palpitations, bleeding, and chest pain).

Socio-demographic and clinical data will be collected from both groups for comparison, including age, sex, educational level, type of anaemia, primary care centre, the physician responsible for monitoring anaemia, cognitive status, inclusion in the case management program, number of haemogram controls performed via venipuncture.

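### Linear regression with no allowance for person-time is named for hospitalisation and A&E counts, so early exits shrink the difference between arms, or bias it if they differ by arm

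*Protocol article*

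**What the plan says.** The Main objective is to "Compare the number of hospitalizations due to anaemia of patients receiving monthly capillary Hb measurements and those receiving standard venipuncture monitoring". The list of main result variables begins "Number of hospitalizations due to anaemia.Number of A&E visits due to anaemia" and continues with three elapsed times.

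The Statistical analysis section first compares the arms by "mean comparison tests (T-test or similar) or distribution comparison tests (Chi-squared or similar"). Under the label of a predictive model it then says "The result variables will be considered discrete quantitative variables. Multiple linear regression will be used to model the data collected". Randomised participants are "included where data are available for each measurement time point". No rate, person-time or offset appears.

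Observation will not be equally long for everyone. The section on suspending or modifying the interventions says "Participants can leave the study at any time and may withdraw consent". It also says "They will be excluded from the trial in the following cases", listing death, a wish to leave, and palliative care with transfusions rejected. The Sample size section allows for 10% dropout. In the control arm, events come from the clinical records and "a bimonthly phone call to determine how many times they have been hospitalized and visited the A&E during the study period". Questionnaires are given at the first visit, six months and 12 months, but the article does not expressly tie the event counts to 12 months.

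**The concern.** The plan recognises that its outcomes are discrete and then names a model for a continuous response with constant error variance. Counts with many zeros, whose variance grows with their mean, do not behave that way.

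The more consequential gap is exposure. A patient who dies in month two without an admission contributes the same zero as a patient followed admission-free for a year. The difference in raw counts therefore mixes two things: how often patients are admitted, and how long they are observed. The effect estimate for the main objective depends on keeping these apart.

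**Working it through.** **The plan's own figure.** Inputs from Sample size: 60% v 35%, two-sided alpha 0.05, power 80%, 10% dropout, arcsine method.

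- h = 2·asin(√0.60) − 2·asin(√0.35) = 0.506
- n = 2·((1.960 + 0.842)/0.506)² = 61.3, so 62 per arm
- 62/0.90 = 68.9, so 69 per arm and 138 in total

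The stated 138 reproduces. The method is one for proportions, which supports reading 60% and 35% as patients with at least one admission. The shares with no admission are then 1 − 0.60 = 40% and 1 − 0.35 = 65%.

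**Implied means and variances.** The documents give no dispersion, so a range is shown. For a negative binomial with size k, P(0) = (1 + μ/k)^(−k), so μ = k·(P(0)^(−1/k) − 1), and the variance is μ + μ²/k. For Poisson, μ = −ln P(0) and the variance is μ.

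| Assumed distribution | Control mean (variance) | Intervention mean (variance) | Variance ratio |
|---|---|---|---|
| Poisson | 0.92 (0.92) | 0.43 (0.43) | 2.1 |
| Negative binomial, k = 1 | 1.50 (3.75) | 0.54 (0.83) | 4.5 |
| Negative binomial, k = 0.5 | 2.63 (16.4) | 0.68 (1.62) | 10.1 |

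At k = 1 the pooled SD is √((3.75 + 0.83)/2) = 1.51. A normal model would put Φ(−0.538/1.51), about 36%, of the intervention arm below zero admissions.

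**Effect of exits on the raw difference.** Assume one year of follow-up, exit times uniform over that year, and events counted up to exit. Mean follow-up is then 1 − 0.5 × exit fraction: 0.975, 0.95, 0.925 and 0.85 years for 5%, 10%, 15% and 30% exits. At k = 1 the full-year difference is 0.538 − 1.50 = −0.962.

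- 10% in both arms: −0.962 × 0.95 = −0.91
- 30% in both arms: −0.962 × 0.85 = −0.82
- No true effect, 30% control v 10% intervention: 1.50 × (0.95 − 0.85) = +0.15 admissions, a ratio of 0.95/0.85 = 1.12 against the intervention
- No true effect, 15% v 5%: 0.975/0.925 = 1.05

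**Type I error of the linear model** (simulation, 69 per arm, no covariates):

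| Exits, control / intervention | k = 1 | k = 0.5 |
|---|---|---|
| 10% / 10% | 4.5% | 4.9% |
| 15% / 5% | 5.7% | 5.4% |
| 30% / 10% | 7.7% | 6.4% |

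In the last row at k = 1, about 0.8% of the rejections falsely favour the intervention and 7.7 − 0.8 = 6.9% falsely favour control. If the exit rates are swapped between arms, so are these two figures.

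**Standard error and power.** With the planned effect, k = 1 and 10% exits per arm, the empirical SD of the arm difference is 0.252, the average pooled standard error is 0.249, and power is 97.5%. Over the exit scenarios tried with the planned effect, power was 94-99.7% for linear regression and 97.5-99.8% for the negative binomial model with offset. At k = 1 the latter gave a rate ratio of 0.35-0.37 (true value 0.359) in every exit scenario.

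**The case against.** The strongest reply is that linear regression does little damage to the randomised comparison here. With equal arms, the pooled-variance standard error coincides with the unequal-variance one, √((s₁² + s₂²)/n). A reader might infer from the 2- to 10-fold variance ratios that the standard error of the treatment effect is badly wrong; under 1:1 allocation it is not. Nor do negative fitted values distort a difference in means. At the planned dropout, type I error is close to nominal. The 30% v 10% split is not in the documents. All of this stands, and it limits the size of the point.

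The regression is also labelled a predictive model and is not named as the primary test; the t-type comparison may have that role. This is fair, but a t-test on raw counts ignores person-time in the same way. The allowance for similar methods is attached to the univariate tests, not to the regression.

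It can be said that an article leaves offsets to the full analysis plan. That would excuse silence. Here a model is named, and a count model would depart from it.

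Two further readings go too far. Recruitment from March 2018 to December 2023 might suggest widely varying follow-up, but a long accrual period does not make individual follow-up unequal, and the assessment schedule points to 12 months each. Linear regression might also be thought to cover the three-level satisfaction item, but satisfaction is listed apart from the main result variables and is not clearly assigned to that model.

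**Conclusion.** The point holds as a moderate one. The protocol names a poorly fitting model for its two count outcomes and makes no allowance for person-time, although its own exit rules and dropout figure mean that observation time will vary.

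The size depends on exits. At 10% in both arms, the raw difference shrinks by about 5% and error control is intact. At 30% in both arms, it shrinks by about 15%. If exits differ by arm, the difference is biased: about 12% in the mean with type I error of about 7-8% under 30% v 10% (k = 1), and about 5% in the mean with type I error of about 5-6% under 15% v 5%. The direction follows whichever arm loses more time.

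These figures rest on the assumed dispersion, on uniform exit times unrelated to admission risk, and on reading 60% and 35% as patients with any admission. The documents do not support a claim of gross loss of power or of error control.

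**What to change.** Replace linear regression for hospitalisations and A&E visits with negative binomial regression, or Poisson regression with robust standard errors. Use log person-time at risk as the offset, with arm and prespecified baseline covariates as terms. Report the rate ratio with its 95% CI. State that events are counted over 12 months from randomisation in both arms, as the assessment schedule implies, with time at risk ending at death or withdrawal of consent.

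The offset does not remove bias when the reason for leaving is related to admission risk, as death and palliative care may be. Add a sensitivity analysis for these exits, and make sure that each patient's person-time matches the period over which events were actually counted.

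The cost is small: new analysis wording and no added patients or visits. The article does not say that exit dates are recorded, so they would have to be taken from the visits, the bimonthly calls and the clinical records.

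### The regression's covariates are chosen because they differ significantly between arms, and nothing limits them to baseline variables, so a variable changed by the intervention could enter and distort the effect.

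*Protocol article*

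**What the plan says.** All references are to the protocol article. Under Statistical analysis, the univariate step is defined as a comparison of arms: "Univariate comparisons between the intervention group and control group will be performed using mean comparison tests" or distribution tests. The Predictive model paragraph follows: "Multiple linear regression will be used to model the data collected". Its independent variables are found by "taking those that present significant differences in the previously calculated univariate models as independent variables", "in addition to the demographic and clinical variables considered relevant". No candidate list is given, no baseline restriction is stated, and the paragraph does not say that arm is a term. No other model is described for the result variables.

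Under Expected results, the article says "Socio-demographic and clinical data will be collected from both groups for comparison". Most of the items named are baseline descriptors (age, sex, educational level, type of anaemia, centre), but the list ends with "number of haemogram controls performed via venipuncture", for which no time point is given. The separate list of other variables includes "Signs and symptoms of anaemia at monthly visits".

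**The concern.** Read together, the two paragraphs make a variable a regressor because it differs between arms. Two kinds of variable can pass that filter.

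- **A baseline variable.** Allocation is random, so a significant difference is chance. It says nothing about whether the variable predicts the outcome, which is the proper reason to adjust.
- **A variable changed by the intervention.** This is the kind most likely to be selected. Adjusting for it removes part of the effect if it lies on the causal pathway, and can create a spurious effect if it is also driven by admissions or by disease severity.

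The venipuncture count is the clearest candidate for the second kind. The Research question and Main objective set monthly capillary measurement against venipuncture monitoring. A count taken during follow-up would therefore probably differ by arm, and it may rise with admissions. At stake is whether the adjusted coefficient still estimates the effect of randomised assignment on admissions for anaemia.

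**Working it through.** **1. The plan's own figure.** Inputs from Sample size: 60% versus 35% hospitalised, two-sided alpha 0.05, 80% power, 10% dropout, arcsine method.
h = 2·asin(√0.60) − 2·asin(√0.35) = 0.506.
n = 2(1.960 + 0.842)² / h² = 61.3, rounded up to 62 per arm. 62/0.9 = 68.9, rounded up to 69, so 138 in total. This reproduces the plan. The 62 evaluable patients per arm are used below.

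**2. Baseline candidates only.** The comparison list names nine variables. If all nine were independent baseline variables, the chance that at least one is significant at 0.05 would be 1 − 0.95⁹ = 37.0%. In simulation the effect stayed unbiased. With one covariate correlated 0.3, 0.5 or 0.7 with the outcome, type I error under the rule was 4.9%, 4.4% and 3.6%. The cost is some efficiency and the loss of prespecification.

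**3. A follow-up venipuncture count as candidate.** The assumptions, none of which the document gives, are:
- Admissions are negative binomial with dispersion 1, so P(none) = 1/(1 + mean). Means of 0.60/0.40 = 1.50 and 0.35/0.65 = 0.54 reproduce the plan's 60% and 35%. The true difference is −0.96.
- Routine venipunctures are Poisson, 6 per year in control and 6, 5, 4 or 2 in intervention, plus 1 per admission.

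In large samples the adjusted effect is Δy − β·Δv. Here Δy and Δv are the arm differences in admissions and in count, and β is the within-arm slope of admissions on count. The variance of admissions is 1.50 + 1.50² = 3.75 in control and 0.54 + 0.54² = 0.83 in intervention, average 2.29. At 6 versus 4, β = 2.29/(2.29 + 5) = 0.314 and Δv = −0.96 − 2 = −2.96, so the adjusted effect is −0.96 + 0.314 × 2.96 = −0.03. At 6 versus 2, β = 2.29/(2.29 + 4) = 0.364 and Δv = −4.96, which gives about +0.84.

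The table simulates the full rule: a t-test of the count at 0.05, then least squares with the count included if selected. Unadjusted, the estimate is −0.96 and a significant benefit appears in 97% of runs.

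| Routine tests, control vs intervention | Mean estimate under the rule | Significant result, true benefit | False harm, no true effect (both means 1.50) |
|---|---|---|---|
| 6 vs 6 | −0.77 | benefit 89% | about 2% |
| 6 vs 5 | −0.40 | benefit 37% | 17% |
| 6 vs 4 | −0.03 | benefit about 3% | 82% |
| 6 vs 2 | +0.82 | harm 74% | 100% |

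If the count is unrelated to admissions there is no bias: benefit is 97% at equal rates and 68% at 6 versus 2, the loss coming from collinearity with arm.

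**4. A different outcome model.** With Poisson admissions (means −ln 0.40 = 0.92 and −ln 0.65 = 0.43) and a count halved by the intervention and correlated with severity, the rule moved the effect from −0.48 to −0.07 and rejection from 78% to 7%. With no true effect, false harm appeared in 59% of runs, against about 3% unadjusted. A symptom score assumed to carry the whole effect moved the estimate from −0.49 to +0.02.

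**The case against.** The strongest reply has four parts.

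- **The regression is not called primary.** It is headed as a predictive model, and unadjusted arm comparisons are planned first. If these cover the outcomes, an unadjusted randomised comparison will still be reported. This stands: a reader might infer that the main analysis itself is compromised, but the document does not say so. It remains true that this is the only model given for the result variables and that the unadjusted tests sit under descriptive statistics.
- **No candidate list is named, and the venipuncture count has no time point.** It could be a pre-enrolment count, since it closes a list of mostly baseline items. This stands. A reader might infer that the list certainly contains post-randomisation variables, or that the count must differ by design. The document supports neither reading: Intervention does not say venous tests stop in that arm, and nothing says that inpatient tests are counted. Inclusion in case management is equally undated. Monthly symptoms are post-randomisation, but monthly visits are described only for the intervention arm.
- **The size follows from the assumed rates.** This also stands. Removal or reversal needs a sizeable drop in venous testing together with a link to admissions. At equal routine rates the loss is modest.
- **Selection does not invalidate every p-value.** This is correct for baseline covariates, as step 2 shows.

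None of this rescues the rule. It is a stated rule, not a detail left to an unseen analysis plan. It lacks the one restriction that would make it harmless, and its filter favours the variables that should stay out.

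**Conclusion.** The concern holds in a limited form. The article selects regressors by between-arm significance without limiting them to baseline variables, and that is the wrong rule for a randomised trial. Applied to baseline variables alone, it leaves the effect unbiased and mainly costs efficiency and prespecification. Applied to a variable the intervention changes, it can weaken, remove or reverse the estimate: under the assumptions in step 3, from −0.96 to anything between −0.77 and +0.82, or no bias at all if the count is unrelated to admissions. These figures rest on assumed venipuncture rates, on the count being taken in follow-up and on arm being in the model, so they show what is possible, not what will happen. The rule should be fixed, but the documents do not show that the trial's main comparison is already lost.

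**What to change.** In Statistical analysis:

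- Delete the selection of independent variables by significant between-arm difference, and the open-ended addition of variables judged relevant.
- State that arm is always in the effect model, whatever the univariate result.
- Name in advance a short set of prognostic baseline covariates already collected or known at eligibility, for example age, sex, type of anaemia, primary care centre and transfusions in the qualifying year.
- State that nothing measured after randomisation enters the effect model: follow-up venipuncture count, follow-up Hb, symptoms, satisfaction, or case-management enrolment after allocation.
- Report baseline differences descriptively.

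In Expected results, give the time point of the venipuncture count and of case-management inclusion.

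The change is one of wording and leaves the 138 patients as they are. The downside is that a chance imbalance in an unlisted covariate is examined only in a sensitivity analysis.

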### Validity and reliability/rigour

To ensure rigour in the collection of quantitative data, it will be included in a pseudonymized database so that participants cannot be identified, without any additional data, which will be recorded separately using techniques that guarantee it cannot be traced. Data will be stored in a local repository that only the researchers have access to. Participants will be randomly assigned to the groups to avoid any selection bias.

To improve compliance with intervention protocols, the clinical trial supervisor will prepare a report each semester detailing whether or not follow-up visits are being held and properly recorded in the data collection form.

Throughout the trial, if patients who are not in the transfusion circuit are identified, they will be included therein based on the consensus of hospital and primary care professionals.

### Expected results

#### The main result variables are

Number of hospitalizations due to anaemia.Number of A&E visits due to anaemia.Time elapsed between Hb measurement and circuit activation.Time elapsed between Hb measurement and when the transfusion is performed.Time elapsed between Hb measurement and return home.

The specific measurement variable is the Hb level taken with the Veri-Q® haemoglobinometer once a month.

Other variables are:Satisfaction with monthly anaemia monitoring: taken at six and 12 months. Ad hoc questionnaire.Quality of life: measured at the start of the study and six and 12 months. WHOQOL-BREF questionnaire [22, 23].Prescribed medication that might alter Hb or haematocrit levels.Signs and symptoms of anaemia at monthly visits (dyspnoea, asthenia, palpitations, bleeding, and chest pain).

Socio-demographic and clinical data will be collected from both groups for comparison, including age, sex, educational level, type of anaemia, primary care centre, the physician responsible for monitoring anaemia, cognitive status, inclusion in the case management program, number of haemogram controls performed via venipuncture.

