**Methods:**

Randomized controlled trial Capillary haemoglobin will be measured using a haemoglobinometer on a monthly basis in the intervention group. In the control group, the protocol currently in force at the primary care centre will be followed and venous haemoglobin will be measured. Any cases of anaemia detected in either group will be referred to the transfusion circuit of the reference hospital.

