### Secondary objectives

Compare the number of hospital A&E visits due to anaemia of patients receiving monthly capillary Hb measurements and those receiving standard monitoring.

Compare changes in quality of life of patients receiving monthly capillary Hb measurements and those receiving standard monitoring.

Assess satisfaction with monthly haemoglobinometer measurements.

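### The list of main result variables contradicts the single main objective and the sample size: it promotes A&E visits, a secondary objective, and three elapsed times that serve no objective and do not compare the randomised groups

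*Protocol article*

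**What the plan says.** The protocol article's Main objective section names one comparison: "Compare the number of hospitalizations due to anaemia of patients receiving monthly capillary Hb measurements and those receiving standard venipuncture monitoring". The Sample size section follows it: 60% versus 35% hospitalized, alpha 0.05 two-sided, beta below 20%, 10% dropout, 69 patients per arm and 138 in all. The first of the Secondary objectives reads "Compare the number of hospital A&E visits due to anaemia of patients receiving monthly capillary Hb measurements and those receiving standard monitoring".

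Under Expected results, the list of main result variables opens with "Number of hospitalizations due to anaemia.Number of A&E visits due to anaemia.Time elapsed between Hb measurement and circuit activation" and ends with "Time elapsed between Hb measurement and when the transfusion is performed.Time elapsed between Hb measurement and return home". That makes five. Quality of life, also a secondary objective, appears there among the other variables.

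Three statements govern when the elapsed times come into being:

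- Intervention section: when a patient's "haemoglobin level falls below their reference value, the nurse case manager will activate the transfusion circuit". The same section describes the hospital pathway as working "in a specific circuit between health levels created to this intervention".
- Abstract, Methods: "Any cases of anaemia detected in either group will be referred to the transfusion circuit of the reference hospital".
- Intervention section, on the comparator: "Participants in the control group received standard monitoring, the frequency of which is variable, since it is determined by clinical criteria". In the intervention arm, haemoglobin (Hb) is measured monthly.

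**The concern.** The article gives two different answers to the question of which outcome is the main one. The Main objective and Sample size sections say hospitalizations. Expected results says hospitalizations, A&E visits and three time intervals, without order. A&E visits are therefore both secondary and main, and the three times have main status without belonging to any objective. The Hypothesis section does not settle the matter, because it joins A&E visits, hospitalizations and quality of life without ranking them.

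The three times raise a further problem. They are undefined for a participant in whom no low Hb is detected after randomisation, and the chance and timing of detection depend on how often Hb is measured, which is what differs between the arms. The Statistical analysis section describes between-group tests in general terms and does not exclude these times. A difference in them could then be presented beside the hospitalization result as a main finding of a randomised trial, although randomisation does not protect it.

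**Working it through.** **1. Which outcome the sample size supports.** Inputs from the Sample size section: 0.60 versus 0.35, two-sided alpha 0.05, power 80%, dropout 10%, arcsine method.

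- h = 2·asin(√0.60) − 2·asin(√0.35) = 1.772 − 1.266 = 0.506
- n per arm = 2·((1.960 + 0.842)/0.506)² = 61.3, rounded up to 62
- With dropout: 62/0.90 = 68.9, rounded up to 69 per arm, 138 in total

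The stated figure reproduces exactly, for one outcome and one undivided alpha. (The calculation uses the proportion hospitalized whereas the objective is a number of hospitalizations. That is a separate matter.)

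**2. The status of each variable across the article.**

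| Variable | Objectives | Sample size | Expected results |
|---|---|---|---|
| Hospitalizations due to anaemia | main | yes | main |
| A&E visits due to anaemia | secondary | no | main |
| Time to circuit activation | none | no | main |
| Time to transfusion | none | no | main |
| Time to return home | none | no | main |
| Quality of life | secondary | no | other |

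Only the first row is consistent across all three columns.

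**3. What the A&E contradiction could cost in error rate.** Assumption: either hospitalizations or A&E visits could carry the main claim, each at two-sided 0.05, with no effect on either.

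- Independent tests: 1 − 0.95² = 0.0975, about 9.8%
- Correlated test statistics (simulated, jointly normal): about 9% at correlation 0.5 and about 7% at 0.9

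The article gives no correlation, so 0.5 and 0.9 are illustrative. Counting only errors in favour of the intervention, the independent figure is 1 − 0.975² = 4.9%, against 2.5% for one test.

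**4. What keeping both as main outcomes would cost.** Under Bonferroni with two outcomes (alpha 0.025 each), the hospitalization comparison needs 2·((2.241 + 0.842)/0.506)² = 74.2, so 75 evaluable per arm. Then 75/0.90 = 83.3, so 84 per arm and 168 in total. With the planned 62 evaluable per arm, power for hospitalization falls from 80.4% to 71.8%.

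**5. Whether the three times compare the randomised groups.**

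- A time exists only if a post-randomisation Hb lies below the patient's reference value (Intervention) or anaemia is detected (abstract).
- Detection follows a monthly schedule in one arm and clinical discretion in the other. The arm therefore influences who contributes a time, how often, and how far Hb has fallen by then.
- The Statistical analysis section includes all randomised participants for whom data are available. That cannot restore comparability when the existence of the data depends on arm.
- The abstract sends detected cases in both arms to the transfusion circuit, while the Intervention section says a circuit was created for the intervention and the Discussion says no direct one existed before. Whether activation denotes the same event in controls is unclear, and these passages must be reconciled.

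**6. What the clock measures.** It starts at the Hb measurement. The Background gives five seconds for a device reading, and the Discussion puts the delay for a laboratory haemogram at sometimes up to 12 h. Time to activation can therefore differ by hours through assay turnaround alone. The interval before measurement, which monthly testing is meant to shorten, is not counted.

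**The case against.** The strongest reply is that the document already contains the answer. It has one main objective, its stated purpose is to reduce hospital admissions, and the sample size fits hospitalization only. The heading in Expected results never uses the word primary and may simply introduce a list of variables to collect. The Discussion says the study will assess the transfusion circuit and the hospital's speed of response, so process measures have a natural place. Fast results are also the intended mechanism, not a defect. All of this stands, and it makes the fix easy, but it does not remove the contradiction in the text.

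A reader might infer that the trial may succeed on any of the five variables, each tested at 0.05, and that the type I error of its headline claim is therefore not 5%. The document does not support that. No success rule is stated, and 0.05 appears only in the sample-size calculation for hospitalization. The corresponding five-test figure, 1 − 0.95⁵ = 22.6%, should not be used. It needs five independent true null hypotheses, but the three times share a starting point and run in sequence, and time to activation is expected to differ through turnaround alone.

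Two further limits apply. Eligibility requires two or more transfusions in a year, so many participants may have a circuit event. That would shrink the selection problem without removing it, and its size cannot be calculated from the article. A multiplicity method and the handling of repeat activations may properly be left to the analysis plan, so their absence is not part of this point.

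**Conclusion.** The point holds as an internal contradiction. Expected results conflicts with the Main objective, Secondary objectives and Sample size sections on which outcomes are main, and no ranking is given. That follows directly from the text.

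The error-rate consequence is conditional. It is about 9.8% at most for hospitalizations plus A&E visits, assuming an either-one rule at two-sided 0.05 and independent tests, and lower if the two are positively correlated. If hospitalization is kept as the only main comparison, its alpha is the stated 0.05.

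The three elapsed times are conditional on a post-randomisation event whose detection depends on arm, so they cannot serve as randomised evidence of efficacy. This rests on the stated measurement schedules and needs no numerical assumption, but the amount of bias is unknown. The 12 h figure is an occasional maximum and bears mainly on time to activation, since the other two times also depend on hospital steps. The text should be corrected before analysis.

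**What to change.** In Expected results, name the number of hospitalizations due to anaemia as the sole primary outcome, in line with the Main objective. List A&E visits and quality of life as secondary outcomes, in line with the Secondary objectives. Move the three elapsed times to a separate group of process measures, reported descriptively by arm among participants with a circuit event, with a statement that they are not evidence of efficacy. Reconcile the abstract and the Intervention section on whether the circuit applies to both arms, so that the meaning of activation in controls is clear.

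The change is one of wording. The sample size stays at 138 and no data collection changes. The cost is that fewer outcomes can be claimed as main results.
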